### Recruitment {15}

Participants will be recruited in eight waves of 20 participants each. Recruitment will be advertised in notices posted in the clinic and on a social network platform (WeChat). The main inclusion and exclusion criteria will be included in our registration questionnaire. Possible eligible participants will be invited to come to the hospital for a physical examination and baseline assessment. Eligible participants will be assigned a number according to the sequence of their arrival at the hospital and a to the research assistant ([name]) for random grouping. Participants will be informed of the time of treatment after baseline assessment, so that the participants could arrange the time. Treatment content will be announced 3 days before the start of the intervention.

### Assignment of interventions: allocation

#### Sequence generation {16a}

For the randomization, a simple block randomization process was conceived and will be implemented by a trial assistant ([name]). After eligibility is confirmed, every participant will be assigned a unique number as an identifier. Sequence generation will be achieved using the IBM Statistical Package for Social Sciences (SPSS) version 23 software and stratified with a 1:1 allocation random block size of 10. The randomization list reports a progressive randomization number for randomized participants (from 1 to 20), and the treatment (SCE or combined SCE + CST) will be assigned to the subject in either group.

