## Methods: participants, interventions, and outcomes

### Study setting {9}

The study site is located in the outpatient Department of Rehabilitation of the First Affiliated Hospital of Sun Yat-sen University, and participants in Guangzhou will be mainly recruited for the study.

The form of intervention will be group intervention with 10 participants per intervention combined group.

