## Statistical methods

### Statistical methods for primary and secondary outcomes {20a}

We will use an intent-to-treat approach to analyze all available data at baseline, post-treatment, and 3 months. We will compare the baseline demographic and clinical characteristics of the groups using the independent *t*-test for continuous variables and chi-square tests for categorical variables. The primary endpoint is change in RMQD during 3 months. Analyses of the primary and secondary continuous outcome variables will be analyzed using two-way repeated-measures ANOVA. The effect sizes of the mean group differences will be calculated as the Cohen *d*. Differences with a 2-sided *P*-value < 0.05 will be considered significant. All data will be analyzed using IBM SPSS Statistics V.22.

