## Discussion

This trial attempts to combine SCT with CSE to improve the treatment of NCLBP. Since SCT not only relieves the negative emotions of patients with low back pain but also promotes healthy behaviors, we think it is therefore likely to improve the effect of CSE in treating NCLBP. A face-to-face intervention will only occur once a week; for the rest of the time, we will use social networks to communicate with the subjects. However, due to the influence of COVID-19, our face-to-face treatment may be suspended at any time, so we will consider developing an app for remote treatment in the future, making the treatment safer and more convenient for the participants.

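### Allocation is called stratified but no factor is named, and the two-way ANOVA omits recruitment wave, the balancing factor the list implies: a small loss of precision, no bias

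*Protocol article*

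**What the plan says.** All references are to the Protocol article.

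- **Sequence generation {16a}** opens with "a simple block randomization process was conceived and will be implemented by a trial assistant". It then describes the sequence as "stratified with a 1:1 allocation random block size of 10". No stratification factor is named there, and Trial design {8} mentions only block randomisation at 1:1.
- The same section gives the length of the list: "The randomization list reports a progressive randomization number for randomized participants (from 1 to 20".
- **Recruitment {15}**: "Participants will be recruited in eight waves of 20 participants each".
- **Study setting {9}**: "The form of intervention will be group intervention with 10 participants per intervention combined group".
- **Statistical methods {20a}**: "The primary endpoint is change in RMQD during 3 months", and "Analyses of the primary and secondary continuous outcome variables will be analyzed using two-way repeated-measures ANOVA". No wave, stratum or other covariate is named there, nor in the sections on additional analyses {20b} and missing data {20c}.
- **Trial status** puts recruitment between 15 April 2021 and 30 October 2023. The **Discussion** warns that, because of COVID-19, "our face-to-face treatment may be suspended at any time".

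**The concern.** When allocation is balanced within the levels of a factor, the factor's effect on the outcome cancels from the difference between arms. An analysis that leaves the factor out still counts its variation as noise, so it reports a larger standard error than the design produces. The design has secured some precision and the analysis gives it away.

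Two things prompt the question here. First, a sequence called both simple and stratified, with no factor named, leaves nobody able to say which term a matching analysis needs. Second, the one grouping that fits the list is the wave, and the planned model has no place for it. Waves are spread over roughly two and a half years with possible interruptions of face-to-face sessions, so it is plausible, though not shown, that improvement differs from wave to wave.

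**Working it through.** **1. What the list implies.** Twenty numbers in blocks of 10 are two complete blocks. With 5:5 in each block that gives 10:10, which matches one wave of 20 and one combined group of 10. It is a single-site trial, and no patient characteristic is tied to allocation, so no other grouping in the document fits. This remains an inference. The counts also do not close: 8 × 20 = 160, not 166, and 166/20 = 8.3, so complete waves cannot give the target.

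**2. The plan's own sample size.** Inputs from Sample size {14}: mean changes 5.5 and 3.1 (difference 2.4), SDs 4.7 and 4.8, two-sided alpha 0.05, power 80%.

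- Pooled SD = √[(4.7² + 4.8²)/2] = 4.75.
- Normal approximation: n = 2 × [4.75 × (1.960 + 0.842)/2.4]² = 61.5, so 62 per arm. The noncentral t gives 63.
- Dividing 63 by 0.955, the efficiency of the Wilcoxon test, gives 65.97, so 66. The protocol does not say that this route was used. The t-test has 82.1% power at 66 per arm.
- Dropout: 66/0.8 = 82.5, so 83 per arm and 166 in total.

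The figure is on the safe side and does not depend on the present point.

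**3. Which wave variation matters.** The primary endpoint is a change, tested through group by time. A wave whose patients are worse at every visit drops out within subjects. Only differences between waves in the amount of change remain. Write ρ for the share of the variance of change that lies between waves and is common to both arms. The document gives no value, so 0 to 0.20 is taken as an assumed range.

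**4. Standard errors.** Take 8 waves with 8 completers per arm in each (10 less 20%), so n = 64 per arm.

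- True SE of the difference = 4.75 × √[2(1 − ρ)/64].
- Expected squared SE without wave: the wave part of the within-arm sum of squares has expectation 8 × 7 = 56 wave variances, over 63 degrees of freedom. So the variance used is 4.75² × [1 − ρ(1 − 56/63)] = 4.75² × (1 − ρ/9).
- Overstatement = √[(1 − ρ/9)/(1 − ρ)] = 1.009, 1.023 and 1.048 at ρ = 0.02, 0.05 and 0.10.

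**5. Simulation.** Change scores with total SD 4.75 and difference 2.4, 40,000 runs per scenario. A t-test without wave (126 degrees of freedom) is compared with a model with a fixed wave term (128 − 8 − 1 = 119).

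| Assumed ρ | Type I error without wave | with wave | Power without wave | with wave |
|---|---|---|---|---|
| 0 | 5.1% | 5.1% | 80.7% | 80.7% |
| 0.02 | 4.7% | 5.0% | 81.2% | 81.6% |
| 0.05 | 4.6% | 5.0% | 81.7% | 82.9% |
| 0.10 | 4.1% | 5.1% | 82.2% | 84.5% |
| 0.20 | 3.1% | 5.0% | 84.4% | 88.8% |

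The simulated mean SE without wave against the true SE is 0.835 against 0.816 at ρ = 0.05 (ratio 1.023) and 0.833 against 0.799 at ρ = 0.10 (ratio 1.043). This agrees with step 4 within simulation error.

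**The case against.** **Blocking by wave is not stated.** A reader might infer that the protocol stratifies by wave and then contradicts itself in the analysis. It does not say that. The word stratified appears once in that section, without a factor, next to the word simple, and may be loose wording for blocking. This stands: what is certain is the unnamed factor, and the mismatch with the analysis is conditional on the inferred reading.

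**Covariates are commonly left to the analysis plan.** This limits the weight of the point. It does not remove it, because a two-way model in a two-arm trial with repeated visits fixes the factors as group and time.

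**Not all wave variation is lost.** It is tempting to say that wave differences as a whole stay in the error. Stable differences in level do not affect the group-by-time test; they matter only for the between-subject group effect.

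**The gain is easily overstated.** Setting adjusted power at 66 per arm (82.9%, 84.0%, 85.9% at ρ = 0.02, 0.05, 0.10) against one fixed unadjusted 82.1% suggests gains of 0.8, 1.9 and 3.8 points. But balance within waves also reduces the true variance of the unadjusted estimate, so its power rises with ρ too. The like-for-like gains are 0.4, 1.2 and 2.3 points.

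**The direction is not secure for the trial as a whole.** A reader might conclude that the planned test errs on the safe side. That follows only for wave effects common to both arms. The combined treatment is given in groups of 10, one per wave on this reading. Effects specific to such a group can make the unadjusted standard error too small, and a wave term does not remove them.

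**Conclusion.** The point holds in a limited form. The protocol calls its sequence stratified without a factor. If the list is applied wave by wave, as its length suggests, the planned model omits the factor that was balanced. The result is a slightly large standard error and a slightly conservative test for wave effects that both arms share, with no bias in the treatment estimate.

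The size is small. With a wave share of 5% to 10% the loss is about 1 to 2 points of power; at 2% or less it is under half a point. These figures rest on an assumed wave share, on equal numbers of completers per arm in every wave, and on a single change score in place of the full three-visit ANOVA. This is a worthwhile refinement, and it does not threaten the trial's conclusions.

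**What to change.** - In Sequence generation {16a}, name the stratification factor or delete the word stratified. State whether the blocks sit inside waves, and reconcile eight waves of 20 with the target of 166.
- In Statistical methods {20a}, add wave (or the factor that is named) as a between-subject factor crossed with time. Equivalently, enter it as a fixed factor in a model for change. A wave main effect that is not crossed with time would leave the group-by-time contrast as it is.
- Handle clustering by treatment group within an arm separately.

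The cost is a sentence or two and one extra factor, about 7 degrees of freedom (126 to 119 in the calculation above), with no new data. In the simulation the term cost no visible power when waves do not differ (80.7% either way).

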#### Concealment mechanism {16b}

For allocation concealment, the randomization list will be maintained by the trial assistant ([name]) who would not participate in the entire treatment procedure.

#### Implementation {16c}

The trial assistant ([name]) who was not involved in the entire treatment procedure generated and maintained the allocation sequence. The principal investigator ([name]) enrolled and assigned the participants to the groups according to their unique numbers. Once allocated, the participant was not allowed to change their groups.

#### Procedure for unblinding if needed {17b}

Not applicable. There is no need for unblinding.

### Data collection and management

#### Plans for assessment and collection of outcomes {18a}

The data will be collected by the electronic questionnaire and automatically stored in the network disk database (https://mhlab7.wjx.cn/corplogin.aspx). The data will be jointly managed by the research team and analyzed by the statistical analyst, who will not know the grouping situation and intervention measures.

#### Plans to promote participant retention and complete follow-up {18b}

At the time of baseline assessment, participants will be charged a deposit of 100 yuan, which will be returned upon completion of the follow-up. The participants must complete two follow-up visits to receive their deposit (20 yuan for the first visit and 80 yuan for the second).

#### Data management {19}

Data will be collected from participants using the electronic questionnaire; they will fill in the form themselves according to the instructions. The data will be stored directly in the network disk of Wenjuanxing (https://mhlab7.wjx.cn/corplogin.aspx). After the patient fills it out, they are not allowed to modify it. The musculoskeletal ultrasound and fMRI data will be input into the computer by two people independently and then checked by a third one. If there is any inconsistency, it needs to be discussed and confirmed.

#### Confidentiality {27}

The personal information and confidentiality of the participants will be protected before, during, and after the trial. In all the saved data, only the unique number identifier of participants will be displayed, not the name of the participants. Only the researcher knows the name corresponding to the number.

#### Plans for collection, laboratory evaluation, and storage of biological specimens for genetic or molecular analysis in this trial/future use {33}

Not applicable. No biological samples will be collected for genetic or molecular analysis as part of this trial.

## Statistical methods

### Statistical methods for primary and secondary outcomes {20a}

We will use an intent-to-treat approach to analyze all available data at baseline, post-treatment, and 3 months. We will compare the baseline demographic and clinical characteristics of the groups using the independent *t*-test for continuous variables and chi-square tests for categorical variables. The primary endpoint is change in RMQD during 3 months. Analyses of the primary and secondary continuous outcome variables will be analyzed using two-way repeated-measures ANOVA. The effect sizes of the mean group differences will be calculated as the Cohen *d*. Differences with a 2-sided *P*-value < 0.05 will be considered significant. All data will be analyzed using IBM SPSS Statistics V.22.

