**Methods:**

In this study, we will randomize 166 adults with NCLBP to a combined SCT and CSE arm or a CSE alone arm (83 participants per group). Both interventions will consist of four weekly 1.5-h group sessions of CSE supplemented by home practice. The combined group protocol also includes 2 h of SCT before CSE. Interviewers masked to the treatment assignments will assess the outcomes at 4 and 16 weeks post-randomization. The primary outcomes are back pain disability (based on the Roland-Morris Disability Questionnaire) and pain intensity (NRS; average pain, worst pain, average pain) at 16 weeks.

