### Trial design {8}

The trial was designed as a randomized, controlled, observer- and patient-blinded trial with two parallel groups. Randomization will be performed as block randomization with a 1:1 allocation. The control group will receive CSE only while the intervention combined group will receive a combination of CSE and SCT. Participants will be asked to complete a follow-up assessment at weeks 4 (post-treatment) and 16 (primary end point) after randomization (Fig. 1).

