### Outcomes {12}

Participants will complete the outcome assessment at baseline, the end of the 4th week, and the follow-up 16 weeks after baseline evaluation. Baseline data collection included demographic and clinical characteristics, such as gender, age, work status, height, weight, education, treatment history, and medical history. Participants scanned the QR code to complete the questionnaire by themselves.

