#### Primary outcomes

The primary outcomes are disability associated with low back pain and pain intensity.

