##### Pain intensity

Pain intensity will be assessed with the Numeric Rating Scale (NRS), which measures the mean pain intensity during the last week (scale 0–10, higher scores indicate greater pain intensity) [24]. We selected three NRS types: average NRS (average pain intensity over the last week), current NRS (current pain intensity), and most severe NRS (most severe pain intensity over the last week) [16].

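### The primary endpoint is RMDQ alone in the main statistical section and sample size, but RMDQ plus three pain scores elsewhere, with differences judged at 0.05

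*Protocol article*

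**What the plan says.** **Which variables are primary.**

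- Statistical methods {20a} names a single endpoint: "The primary endpoint is change in RMQD during 3 months".
- Sample size {14} uses RMDQ only.
- Primary outcomes names two domains: "The primary outcomes are disability associated with low back pain and pain intensity".
- Pain intensity splits the second domain into three scores: "We selected three NRS types: average NRS (average pain intensity over the last week), current NRS (current pain intensity), and most severe NRS".
- The abstract lists RMDQ and "pain intensity (NRS; average pain, worst pain, average pain) at 16 weeks". Table 3 also puts RMDQ and NRS under the primary heading, with the same NRS list.
- Additional analyses {20b}, in the same chapter as {20a}, again calls RMDQ and NRS the primary outcomes.

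**Which NRS scores.** The abstract and Table 3 name average pain twice, name worst pain once, and omit the current pain that the Pain intensity section includes.

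**When.** Trial design {8} places follow-up at "weeks 4 (post-treatment) and 16 (primary end point) after randomization". Outcomes {12} has "the follow-up 16 weeks after baseline evaluation". Sections {20a} and {21b} speak of three months without giving an origin.

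**Test level.** Section {20a} applies two-sided 0.05 to differences and gives no order, alpha split or rule for combining primary outcomes.

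**The concern.** A reader cannot tell from this document whether the trial has one primary variable or four. The answer decides what the 5% error rate covers, what the 80% power refers to, and which result the final report may call its primary finding. The interim analysis in {21b} is run on the primary endpoint and can lead to the trial being continued, modified or halted, so it inherits the ambiguity.

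With several scores called primary in some sections and one in another, the choice could be settled after results are known: RMDQ if it succeeds, or whichever pain score does. The mixed NRS list and the three visit labels add to this, because they leave the exact variable and time point open to interpretation.

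**Working it through.** **1. Reproduce the stated sample size.** Inputs from {14}: RMDQ change 5.5 (SD 4.7) against 3.1 (SD 4.8), two-sided alpha 0.05, power 80%, 1:1 allocation, 20% dropout.

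- Difference: 5.5 − 3.1 = 2.4. Pooled SD: √((4.7² + 4.8²)/2) = √22.565 = 4.750. Standardised difference: 2.4/4.750 = 0.505.
- Normal approximation: n = 2 × (1.960 + 0.842)² × 22.565/2.4² = 61.5, so 62 per arm. Exact two-sample t-test: 62.5, so 63.
- Dividing the t-test figure by 0.955, the usual Mann-Whitney efficiency, gives 65.4, so 66. This matches the plan, although the article does not name that test.
- Dropout: 66/0.80 = 82.5, so 83 per arm and 166 in total, as stated.

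The size is therefore adequate for one test of RMDQ at 0.05. By t-test, 66 per arm gives 82% power. Nothing in the calculation concerns NRS.

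**2. Count the primary variables on each reading.**

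| Reading | Source | Number |
|---|---|---|
| RMDQ alone | {20a}, {14} | 1 |
| Two domains | Primary outcomes, {20b} | 2 |
| RMDQ, average and worst NRS (literal list) | Abstract, Table 3 | 3 |
| RMDQ, average, current and worst NRS | Pain intensity section | 4 |

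**3. Chance of at least one false positive if any single success counted, each test at 0.05.** For independent tests this is 1 − 0.95^k:

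- k = 1: 5%
- k = 2: 1 − 0.9025 = 9.75%
- k = 3: 1 − 0.8574 = 14.3%
- k = 4: 1 − 0.8145 = 18.5%

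The scores are surely correlated, but the article gives no correlations. Simulating four normal statistics with an assumed common correlation (1,000,000 draws, |Z| > 1.96) gives:

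| Assumed correlation | 0.3 | 0.5 | 0.7 | 0.9 |
|---|---|---|---|---|
| At least one false positive | 17.4% | 15.6% | 13.1% | 9.3% |

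**4. Cost of keeping several primaries under an either-or rule with Bonferroni (t-test basis, RMDQ effect as above).**

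| Family | Alpha per test | Evaluable per arm | With dropout | Total | RMDQ power at 66 per arm |
|---|---|---|---|---|---|
| RMDQ alone, as planned | 0.05 | 66 | 83 | 166 | 82% |
| Two domains | 0.025 | 76 | 95 | 190 | 74% |
| Four scores | 0.0125 | 89 | 112 | 224 | 64% |

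If all primaries had to succeed, the type I error would not inflate, but the power of the whole claim would be below that for RMDQ alone.

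**5. Timing labels.** Treatment lasts 4 weeks, and Table 3 has only two post-baseline assessment points, weeks 4 and 16. Three months (12 weeks) after a 4-week treatment is 4 + 12 = week 16. Three months counted from randomization would fall near week 13, where no visit is planned. The labels can be reconciled, but only by inference.

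**The case against.** **Read as a whole, the plan has one primary endpoint.** Section {20a} uses the singular and {14} powers RMDQ alone, so the primary error is 5%. Multiplicity rules commonly sit in an analysis plan, which is not shown here. Part of this stands: the absence of a multiplicity procedure is not itself the finding. But the contradiction lies within this document. Section {20b} returns to two primary outcomes shortly after {20a} names one, and an analysis plan cannot tell a reader which statement the protocol meant.

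**The inflated error rates need a rule the protocol never states.** This stands. A reader might infer that the trial will claim success on any one of four scores. The text does not say so; it leaves the question open. The 9% to 18.5% figures show what that reading would cost and are not the trial's established error rate.

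**The duplicated average pain is a copying slip.** Probably so, since the Pain intensity section defines the three scores clearly. It is minor, but it affects an item listed as primary.

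**Three months and 16 weeks can be the same visit.** This also stands. The labels need aligning, but two different primary time points have not been shown.

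**A stronger timing reading is tempting.** Because participants are recruited in waves of 20, one might infer that visits counted from baseline fall before treatment is complete for early arrivals. The documents do not support this. They give no interval between baseline, randomization and the first session. Dividing the recruitment window by eight waves to get a waiting time would assume steady, even accrual that is nowhere described. Table 3 records class attendance in weeks 1–4, and {8} calls week 4 post-treatment, so the planned calendar starts with treatment.

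**Conclusion.** The inconsistency is real and should be corrected. The current text names one primary variable in {20a} and {14}, and two domains with up to four scores in the abstract, the outcomes sections, Table 3 and {20b}.

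Only the RMDQ-alone reading keeps the primary error at 5% and agrees with the sample size of 66 evaluable and 83 enrolled per arm. Under an any-one-of-four rule, the error would be 18.5% if the tests were independent, and 17.4% down to 9.3% for assumed common correlations of 0.3 to 0.9. These figures depend on that rule and on correlations the article does not give.

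The NRS listing and the visit labels are secondary inconsistencies. They need correcting, but they do not show mistimed visits or a diluted effect.

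**What to change.** - In every section, name change in RMDQ from baseline to week 16 as the sole primary endpoint, tested at two-sided 0.05. This affects the abstract, the primary outcomes section, Table 3, {20a} and {20b}.
- Make average NRS the first key secondary, tested only if RMDQ is significant. List worst and current NRS as other secondary outcomes.
- In the abstract and Table 3, replace the second mention of average pain with current pain.
- Label the late visit as week 16 after randomization throughout, including {12}, {20a} and {21b}. This aligns the wording with {8} and does not move the visit clock to the first treatment session, which would change procedure.
- Make the change by formal amendment under {25} before any comparative look at the data, including the interim after the first 20 participants. Recruitment opened in April 2021 and the article does not say whether that look has taken place. If it has, the amendment should say so.

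**Cost.** The sample size stays at 66 evaluable and 83 enrolled per arm, 166 in total. The price is an amendment with ethics approval and the loss of primary status for NRS. If the investigators want NRS to remain primary, they must state the success rule and re-size the trial; for an either-or rule with Bonferroni, that means about 190 participants for two domains or 224 for four scores. The NRS side of that calculation would need its own inputs, which the article does not give.
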